## Abstract

**Background:**

Intermediaries are health-related workers who facilitate connections to local physical activities. Intermediaries deliver interventions by receiving referrals, conducting assessments, connecting referred individuals to activities and/or services in the community, and following up with them over time. However, it is unclear whether individuals who are referred to physical activities by an intermediary improve their physical activity levels, and what their perspectives and experiences are of participating in this intervention. To date there has been a lack of studies investigating the effect of this intervention on physical activity using appropriate outcome measures.

**Methods:**

This will be a mixed methods pilot feasibility study. Participants will be individuals referred or self-referred to an intermediary and connected to local physical activities. Participants will be recruited through two types of intermediary services in Ireland; social prescribing and local sports partnerships. A total of 30 participants will be recruited (15 per service). Baseline demographic information will be taken upon enrolment to the study and three questionnaires will be completed: the International Physical Activity Questionnaire - Short Form, Self-Efficacy for Exercise Scale and Short Warwick Edinburgh Mental Well-being Scale. The questionnaires will be repeated after 12 weeks and in addition semi-structured interviews will be carried out to explore intervention content and delivery, as well as acceptability of the intervention and evaluation design.

**Discussion:**

This overall aim of this proposed study is to investigate the feasibility of an intervention delivered by an intermediary to improve physical activity and health-related outcomes of community-dwelling individuals.

**Registration:**

ClinicalTrials.gov (NCT06260995).

## Introduction

1

Physical inactivity is a major global issue affecting health. Physical activity, sport and exercise resources in the community (local physical activities) offer choice, reduce barriers to participation and improve adherence [[1], [2], [3]]. An ‘intermediary’ is a health-related worker who supports individuals to improve their health and wellbeing. Intermediaries facilitate connections to community resources, services and supports (including local physical activities) to improve health and wellbeing [[4], [5], [6], [7], [8]]. A scoping review of methods used to connect individuals from primary care to local physical activities found strong positive findings for processes that involved referral to an intermediary, when examining the percentage of patients connected with a physical activity opportunity, the percentage of connected patients enrolling in and attending the first session of the physical activity, and acceptability of the intermediary service for primary care professionals and patients [9]. Another rapid scoping review of social prescribing link workers (a type of intermediary) found improvements in physical activity levels and quality of life and/or wellbeing [3].

Intermediaries deliver complex interventions due to the number of components involved, the expertise and skills required by those delivering the intervention, the number of groups targeted and the level of flexibility of the intervention components [10]. When reporting and evaluating complex interventions, it is essential that the contextual factors and causal mechanisms are understood [11]. While interventions are being delivered by intermediaries to facilitate engagement in physical activity, the processes involved in the intermediary ‘intervention’ have been poorly described. For example, the processes of referral/connection to an intermediary, the characteristics of the intermediaries themselves, the profile of individuals referred to an intermediary, the mechanisms of actions/strategies used to connect individuals to local physical activities and the local physical activity opportunities accessed remained unclear [12,13].

To date, the research team have completed a scoping review of the published literature to describe the processes of an intermediary when connecting community-dwelling individuals to local physical activities [14]. This review found many different approaches to establishing this connection, and often the processes of referral, assessment, follow-up, and discharge were poorly described. In order to address these gaps, a qualitative descriptive study was carried out where intermediaries from three different professions across Ireland were interviewed; health promotion and improvement officers, local sports partnership community sports development officers and social prescribing link workers [15]. The aim of this study was to gain insight into the role of intermediaries in Ireland and to further define the processes, practices and procedures in the Irish context.

The two previous studies helped to determine the processes of the ‘intervention’ delivered by an intermediary, i.e., receive a referral or self-referral, conduct an assessment, connect to a local physical activity, followed by a period of follow-up and subsequent discharge from the intermediary service. Based on the results from the scoping review and the qualitative descriptive study, there remained three main evidence gaps: 1) after the individual connects to local physical activities, do they continue to engage in physical activity, 2) what are the perspectives and experiences of individuals referred to an intermediary, and 3) is an intervention delivered by an intermediary effective in improving physical activity and wider health-related outcomes? However, to date there has been a limited number of high-quality studies investigating the effectiveness of the intervention delivered by an intermediary, with only five RCTs identified in the scoping review [[16], [17], [18], [19], [20]].

Effective methods of physical activity promotion are needed, as evidenced by the low numbers of people engaging in sufficient physical activity. Globally, over a quarter of adults are physically inactive [21]. In Ireland, rates of physical inactivity are higher than the global average, with 54–66 % of the population failing to meet physical activity recommendations [22,23]. If the intervention delivered by an intermediary was shown to be effective, it could be a promising method of improving physical activity levels. When evaluating complex interventions, feasibility testing is recommended in order to make decisions about progression to the evaluation phase [10]. Having identified the core elements and contextual factors of interventions delivered by an intermediary in Ireland, the research team are now progressing to the next phase of the study which includes feasibility testing.

A feasibility study asks whether a research study can be done, should we proceed with it, and if so, how [24]. Four feasibility studies were identified in the scoping review, and while all studies found their evaluation designs and interventions to be feasible, none of these studies were carried out in Europe limiting their transferability to the Irish context. The majority focused on clinical populations, and a wide variety of outcome measures were used to assess physical activity and health-related outcomes [[25], [26], [27], [28]]. There is a need therefore to determine appropriate physical activity and health-related outcome measures as well as appropriate evaluation designs relevant to the Irish context and a community-dwelling population, before full-scale evaluations can be carried out. There is also a need to investigate the experiences of those who undergo an intervention delivered by an intermediary. Therefore, the purpose of this proposed study is to examine the feasibility and acceptability of an intervention delivered by an intermediary to improve physical activity levels and wider health-related outcomes, as well as the feasibility of the evaluation design.

## Materials and methods

2

### Intervention

2.1

The intervention that will be examined in this proposed study consists of two phases. The first is the intervention delivered by the intermediary, and the second is attendance and participation in the local physical activity facilitated by the intermediary. The intervention delivered by an intermediary comprises four main steps; referral to an intermediary, assessment of the individual by the intermediary, connection to a local physical activity, and a follow-up period. How the intervention is delivered by the intermediary varies depending on the type of intermediary, the individual who is referred and their needs in relation to their health and wellbeing, the local context and the availability of community services and supports. Logic models were developed based on findings from the scoping review [14] and qualitative study [15] to describe the steps in the intervention delivered by intermediaries (Fig. 1), and are summarised briefly in the following section.

**Fig. 1 fig1:**
[figure not shown]
Logic Model Describing an Intervention Delivered by Local Sports Partnership Community Sports Development Officers and Social Prescribing Link Workers in Ireland. Data in this logic model is based on the results of the scoping review and qualitative descriptive study conducted as part of this project [14,15], and is based on Sport England logic model guidance [29]. Abbreviations: LSPO – local sports partnership community sports development officers, PA – physical activity, SPLW - social prescribing link workers.

#### Social prescribing link workers [SPLW]

2.1.1

SPLW receive referrals from healthcare professionals, community services, or through self-referral. Individuals are referred for social isolation, for frequent healthcare attendance, complex social needs, or to address a pre-existing mental or physical health issue [30]. SPLW carry out a lengthy in-depth assessment of the individual's needs in relation to their health and wellbeing, and then work with the individual over a number of weeks and months to connect them to a range of community services and supports, which can include local physical activities. They use a number of strategies during this follow-up period, characterised by ongoing instrumental support (doing things for the individual [31]), empowerment and motivation techniques and/or attending activities with the individual [15].

#### Local sports partnership community sports development officers [LSPO]

2.1.2

LSPO mainly receive self-referrals, or can receive referrals, to improve the physical activity levels of individuals through participation in physical activity groups delivered by the local sports partnership [32]. LSPO do not carry out an in-depth assessment, but after the referral is received they may carry out screening and explain/signpost to local physical activities. They use a number of strategies to connect the individual to a local physical activity, such as attending the first session of the local physical activity, providing reassurance and practical support to the individual, as well as keeping them updated and informed as to upcoming local physical activities [15].

After the intermediary establishes a connection to a local physical activity, the individual enrols, attends and takes part in the chosen local physical activity/activities. The intermediary continues to support this engagement during the follow-up period. Local physical activities can include walking groups, local gyms and leisure centres, chair-based exercise, outdoor activities (including gardening), yoga and tai chi amongst others.

### Aims and objectives

2.2

Feasibility is defined as the extent to which a task or innovation can be successfully carried out within a given agency or setting and performed relatively easily or conveniently given existing resources and circumstances [33]. The aim of this proposed study will be to investigate the feasibility of an intervention delivered by an intermediary to improve physical activity and health-related outcomes of community-dwelling adults. Specific objectives include.i.To determine the rate of recruitment and enrolment to the proposed study of individuals who undergo an intervention delivered by an intermediary, which includes participation in local physical activities (intervention participants).ii.To examine the suitability and acceptability of recruitment methods to the proposed study.iii.To determine retention to the proposed study.iv.To describe the demographic and health characteristics of intervention participants.v.To determine participation in and adherence to local physical activities by intervention participants.vi.To explore the acceptability of the intervention delivered by the intermediary.vii.To explore suitability, acceptability, and completion rates of the measurement tools by intervention participants.viii.To assess if change occurs in physical activity and health-related outcomes following participation in the intervention.

The CONSORT extension to pilot and feasibility trials, and the SPIRIT guidelines for protocols of interventional trials have been used to guide the reporting of this protocol [[34], [35], [36]].

### Research ethics approval

2.3

Ethical approval for this proposed study was granted from the Trinity College Dublin Faculty of Health Sciences Research Ethics Committee on August 3, 2023 (Ref: 230603).

### Study design

2.4

This proposed pilot feasibility study (NCT06260995) will use a sequential explanatory mixed methods study design [37]. This design involves collecting and analysing quantitative data, followed by collection of qualitative data to help explain findings from the quantitative data [37,38]. Findings are then merged in the interpretation or discussion sections [37]. The quantitative phase of the study will be a quasi-experimental before-and-after design (without control) and the qualitative phase will employ a qualitative descriptive approach [39].

### Sample

2.5

Participants will be those who are referred or self-referred to a social prescribing link worker or local sports partnership community sports development officer and who undergo an intervention delivered by an intermediary i.e., undergo assessment, onward connection to local physical activities and follow-up. A baseline assessment will be taken upon enrolment on to the study, and this assessment will be repeated after 12 weeks from time of enrolment.

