#### Social prescribing link workers [SPLW]

2.8.1

If the SPLW plans or makes a connection to, and/or the individual referred expresses an interest in attending, a local physical activity, they are eligible for recruitment and they will be informed about the study. This can occur at the time of referral, the first appointment or subsequent appointments. If the potential participant is agreeable, the SPLW will give them a participant information leaflet and informed consent form (study information) and ask consent to share their contact details with the research team. Following a seven-day period, the research team will then contact those who agree to be contacted to screen for eligibility and obtain verbal and written consent to participate, or participants can contact the research team directly.

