#### Local sports partnership community sports development officers [LSPO]

2.8.2

LSPO meet with individuals for the first time at the initial session of a local sports partnership physical activity programme, or during a screening phone call. Every person that the LSPO meets at these initial sessions or during phone calls during the recruitment period will be informed about the study. If the potential participant is agreeable, the LSPO will then give them the study information and ask consent to share their contact details with the research team. The research team will then contact those who agree to be contacted directly after seven days to screen for eligibility and obtain verbal and written consent to participate, or participants can contact the research team directly.

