iv To describe the demographic and health characteristics of intervention participants.	The age, gender, marital status, urban/rural, level of education, ethnicity, employment status, self-reported presence/absence of chronic condition, self-reported rating of health, and types of exercise currently undertaken of the study sample	Data collection form items #1-10	**✘**	**✘** (Items #9–10 only)	
v To determine participation in and adherence to local physical activities by intervention participants.	Changes in types of exercise undertaken by participants from Week 0 to Week 12 - including self-directed physical activity and/or local physical activities accessed as a result of the intervention	Data collection form item #10 - *“What types of exercise do you do currently? Please provide a list.”* Intervention participant semi-structured interview item #3 - Includes prompts about what local physical activities were accessed as a result of the intervention, and adherence to the local physical activity	**✘**	**✘** **✘**	
vi To explore the acceptability of the intervention delivered by the intermediary.	Explore intervention content and delivery by the intermediary, the impact of the support provided, and how acceptable the intervention was to the participant.	Intervention participant semi-structured interview items #1–6, 11 Intervention acceptability NRS (Intervention participant semi-structured interview item #10)		**✘** **✘**	
vii To explore suitability, acceptability and completion rates of the measurement tools by intervention participants.	Determine if the outcome measures used in this proposed study captured important information/improvements made by the participant, the rates of completion of each outcome measure, and explore experience of completing the outcome measures.	Intervention participant semi-structured interview items #7-9 # (%) items completed in data collection form items #1–10, SWEMWBS, SEE, IPAQ and intervention participant semi-structured interview items #1-11	**✘**	**✘** **✘**	
viii To assess if change occurs in physical activity and health-related outcomes following participation in the intervention.	Change in IPAQ-SF score from Week 0 to Week 12 Change in SEE score from Week 0 to Week 12 Change in SWEMWBS score from Week 0 to Week 12 Changes in self-rated rating of health from Week 0 to Week 12	IPAQ-SF SEE SWEMWBS Data collection form item #9	**✘** **✘** **✘** **✘**	**✘** **✘** **✘** **✘**	

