#### Demographics and health status

2.9.1

Participant age, gender, marital status, area in which they live (urban/rural), level of education, ethnicity, employment status, self-reported presence/absence of chronic condition(s), self-reported rating of health, and types of exercise currently undertaken will be collected at baseline. These data will be used to report demographic information and health-related behaviours of the study sample. A number of questionnaires will be completed at baseline (T0), and again after 12 weeks from the time of the baseline assessment (T1), and these are detailed below. Changes in these scores over time will be examined, and these questionnaires will be tested as suitable outcome measures for future studies investigating effectiveness of intermediaries in improving health- and physical-activity related outcomes over time.

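### The 12-week clock starts at enrolment, so the Week 0 to 12 change is not change after participation for everyone

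*Protocol article*

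**What the plan says.** Section 2.1 of the protocol article describes two phases: the intermediary's work, then taking part in the local activity. Baseline (T0) is taken at enrolment. For follow-up (T1), Section 2.5 says "this assessment will be repeated after 12 weeks from time of enrolment" and Section 2.9.1 says "again after 12 weeks from the time of the baseline assessment (T1".

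The two services recruit at different moments:

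- **Social prescribing link workers (SPLW), Section 2.8.1.** A client may be told about the study if the link worker "plans or makes a connection to, and/or the individual referred expresses an interest in attending, a local physical activity". On timing: "This can occur at the time of referral, the first appointment or subsequent appointments". Section 2.1.1 adds that link workers "work with the individual over a number of weeks and months to connect them to a range of community services and supports", of which local physical activities are one possible kind.
- **Local sports partnership officers (LSPO), Section 2.8.2.** Officers meet people "for the first time at the initial session of a local sports partnership physical activity programme, or during a screening phone call". The research team will then "contact those who agree to be contacted directly after seven days to screen for eligibility" and take consent, unless the person gets in touch first.

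Objective viii reads: "To assess if change occurs in physical activity and health-related outcomes following participation in the intervention". Table 2 measures it as the Week 0 to Week 12 change in each score, and Section 2.11 tests it with paired within-group methods. Objective v uses the change in listed exercise types over the same interval (form item #10), together with interview item #3.

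**The concern.** Objective viii is worded as change after people have taken part. The design delivers change over the 12 weeks after enrolment, and these can differ in two directions.

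A client who joins while the connection is only planned may reach T1 with little or no activity behind them. A small change in that person says nothing about the activity.

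A client who joins after the first session has a baseline that is no longer a pre-activity measurement. The IPAQ-SF asks about the last seven days (Section 2.9.2), and item #10 asks what exercise the person does now. Both can already include the programme at T0. Any IPAQ-SF improvement would then be understated, and the new activity would not appear as a change in exercise types.

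Section 2.9.1 also says that the questionnaires are being tried out as outcome measures for later effectiveness studies. Misaligned timing could make a suitable measure look unresponsive.

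**Working it through.** The article gives no figure for the time from enrolment to first session, so there is no stated result to reproduce. The check is timeline arithmetic.

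**Inputs**
- T1 is 12 weeks after T0, and T0 is at enrolment (Sections 2.5 and 2.9.1).
- LSPO client met at an initial session: research contact seven days later (Section 2.8.2), so the first session is normally at week −1 or earlier relative to T0.
- SPLW client: the first session may come before or after T0. The lag is not stated, so the values below are assumptions.
- Target of 30 participants, about 15 per service (Section 2.7).

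**Formulas.** Let s be the week of the first session relative to enrolment.
- Weeks from first session to T1 = max(0, 12 − s).
- Part of that inside the T0 to T1 window = min(12, max(0, 12 − s)).

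| s (weeks) | Weeks from first session to T1 | Inside T0 to T1 |
|---|---|---|
| −4 (assumed) | 16 | 12 |
| −1 (LSPO, met at session) | 13 | 12 |
| 0 (assumed) | 12 | 12 |
| 4 (assumed) | 8 | 8 |
| 8 (assumed) | 4 | 4 |
| 10 (assumed) | 2 | 2 |
| 12 or more (assumed) | 0 | 0 |

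The first two rows share the same 12-week window. For those people the difficulty is not extra exposure at T1 but a baseline taken after the activity began.

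**Sample average.** Suppose all 15 LSPO participants stand at 13 weeks and all 15 SPLW participants share a lag L. The mean is (15 × max(0, 12 − L) + 15 × 13) / 30. For L = 0, 4, 8 and 12 this gives 12.5, 10.5, 8.5 and 6.5 weeks.

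**Dilution, for illustration only.** Assume a standardised change of 0.5 in people who have started, 0 in those who have not, and the SD of change held at 1. With a fraction f not started, the mean standardised change is 0.5 × (1 − f). For f = 0, 0.25 and 0.5 it is 0.50, 0.375 and 0.25. A two-sided paired t-test at 5% with n = 30 (noncentral t) then has power of 75%, 51% and 26%. The article states no effect size or power, so these figures show direction and rough scale, not an expected result.

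**Eligibility wording.** Section 2.5 describes participants as people who go through assessment, connection and follow-up. Section 2.6 and Table 1 require that the intermediary facilitates a connection. Section 2.8.1 lets a plan or an expressed interest suffice for recruitment. The last route admits people who may never be connected by T1.

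**The case against.** The best defence is that a fixed time from enrolment is a sound pragmatic choice for a feasibility study. It keeps people who never start in the sample and suits retention. The number who have started by week 12 is itself feasibility information. The intermediary phase is part of the intervention, so weeks of activity are not the only exposure, and the Discussion already limits conclusions about effectiveness. All of this stands, and it is why the 12-week visit should stay.

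The study also collects relevant information. Interview item #3 covers activities accessed and adherence, exercise types are listed at T0 and T1, and gatekeepers log the date, length and mode of their contacts (Section 2.9.7). It would therefore be wrong to say that someone who has not started could not be recognised. But none of these is described as recording the date of the first session. The forms themselves are not shown, so they may do so.

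Several stronger readings are tempting but unsupported:

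- **Two conflicting anchors.** Baseline is taken at enrolment, so Sections 2.5 and 2.9.1 describe the same clock.
- **A confounded comparison of services.** No objective compares SPLW with LSPO, and Section 2.11 plans within-group tests only.
- **Weeks or months as the delay to activity.** Section 2.1.1 describes work across many kinds of service, not the wait for a physical activity.
- **Enrolment at referral.** Section 2.8.1 allows clients to be informed at referral. The team's contact normally follows seven days later, which shortens any lag after enrolment.
- **Half the sample affected.** Fifteen of 30 is simply the planned SPLW number. Nothing shows that all of them start late.

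**Conclusion.** The point holds as a mismatch between what objectives v and viii claim to measure and what the fixed clock delivers. It does not undermine recruitment, retention or the other feasibility objectives.

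Both ends of the range, 0 and 13 or more weeks, are possible under the recruitment rules as written. The upper end applies only to LSPO clients met at a session and contacted by the team after seven days. Those met on a screening call, or who contact the team sooner, may have less. It is also time since first session, not sessions attended. SPLW clients already connected at enrolment can have the same baseline problem. How many people fall at either end is unknown, and every SPLW lag above is an assumption.

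This is a cheap improvement that should be made, because exact dates are hard to reconstruct afterwards.

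**What to change.** 1. Keep the 12-week visit.
2. Make sure that the gatekeeper log (Section 2.9.7) and interview item #3 capture two dates: connection made and first session attended.
3. Report weeks from first session to T1, with the number already active in the programme at T0 and the number not started by T1.
4. For objectives v and viii, describe change in those groups beside the all-participant result, without testing.
5. State that the all-participant change describes 12 weeks after enrolment, not 12 weeks of participation.
6. Reconcile Sections 2.5 and 2.6 (connection facilitated) with Section 2.8.1 (plan or interest suffices).

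The cost is two date fields in records already kept for each participant, one descriptive table and a few sentences. With about 30 people the descriptive cells will be very small and should be presented as such.
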